#### Primary safety outcomes

The primary safety endpoints in the intervention group are any complications arising from the additional use of IVUS and the requirement for subsequent acute or sub-acute re-intervention (at any time) as a result of the primary intervention.

##### Re-intervention

Freedom from re-intervention will be presented for 1 -year and 5-year follow-up reports. Both superficial and deep venous re-interventions will be recorded.

#### Secondary outcomes

Percentage reduction in ulcer area at 12 weeks, 6 months and 1 yearTime to ulcer healing (days)Bates-Jensen wound assessment tool (BWAT) [18, 19] scores for the index ulcer at 6 weeks, 12 weeks and 6 monthsChanges in Venous Clinical Severity Score [20] at 6 weeks, 3 and 6 months and 1 year.Number of healthcare contacts in the 6 months following the procedureChanges in EQ5D [21] measures of quality of life at 6 weeks, 12 weeks, 6 months and 1 yearUlcer recurrence following healing of the index ulcerUnplanned hospital admission in 6 months following the procedureHealth economic analysis based on generated dataThe number of patients who require additional iliac stenting as a result of additional IVUSThe rate at which patients complete their allocated interventionThe numbers of patients who are compliant with assigned follow-up and wound dressing regimes.The identification of challenges to patient recruitment and follow up compliance

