## Trial design and endpoints

### Statement of design

This is a prospective randomised controlled, assessor-blinded, feasibility trial with participants allocated to one of two parallel groups in a 1:1 fashion. The primary trial centres will be the University Hospital Galway, Ireland, and Singapore General Hospital with further centres currently being evaluated for inclusion. Both the Departments of Vascular Surgery and Interventional Radiology will conduct the trial in unison with equal oversight. Suitable patients shall be recruited from both the outpatient and inpatient setting.

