#### Ulcer assessment

The ulcer will be evaluated by an assessor who has been blinded to the treatment allocation of the patient. Wound size will be calculated using digital planimetry and recorded as cm^2^. Wound assessment will be evaluated using the Bates-Jensen wound assessment tool which has been validated for use in venous leg ulcer assessment [18, 19]. Ulcers that heal prior to intervention will be analysed with intention to treat (Fig. 1).

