## Statistical considerations

Once randomisation and intervention is complete, patient outcomes will be assessed using an intention-to-treat analysis. All losses to follow-up at any time-point will be recorded and reported. A research statistician will conduct all analyses independently. Statistical analysis will be conducted using SPSS Version 21 (IBM Corp, Aramonk, NY) The primary feasibility outcome will be reported as the percentage of all eligible patients who agree to participate in the feasibility study. Descriptive data will be provided at baseline and at each follow-up to define variations among and within groups. Continuous data will be presented as mean and standard deviations with confidence intervals of 95%. Categorical data will be reported as frequencies with chi-square or Fischer’s exact *t* test used for comparative data. Where data is not normally distributed, non-parametric tests will be utilised as applicable. Further subgroup and regression analyses will be undertaken to adjust for confounding variables known to affect ulcer healing including age, duration, mobility and size. A *p* value of < 0.05 will be deemed significant.

Contemporary data suggests a median healing time of about 20 weeks for patients with a venous ulcer treated by superficial venous ablation [23]. Assuming a median time to healing in the control arm (those treated with superficial venous ablation and compression alone) of 140 days would be reduced to 110 days by the addition of iliac vein intervention where necessary (i.e. a 20% relative reduction in healing time) would require 270 patients in each arm of the trial, i.e. 540 in total. Allowing for a 10% withdrawal and dropout rate increases the required sample size to 594 patients. In advance of undertaking such a large trial, we aim to undertake a feasibility phase in order to assess eligibility, recruitment rates and provide baseline data for a refined sample size calculation. For this feasibility phase, we aim to recruit 30 patients to each trial arm.

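### VCSS and EQ5D outcomes are defined as changes with no own-baseline covariate named, and percentage ulcer reduction falls under a mean-and-SD summary that one enlarging ulcer can dominate (minor)

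*Protocol article*

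**What the plan says.** All references are to the protocol article.

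- **Secondary outcomes** lists the change in VCSS "at 6 weeks, 3 and 6 months and 1 year", the change in EQ5D at 6 weeks, 12 weeks, 6 months and 1 year, and the percentage by which ulcer area has fallen at 12 weeks, 6 months and 1 year.
- **Baseline patient data** includes VCSS and EQ5D. Under **Ulcer assessment**, in the same part of the article, "Wound size will be calculated using digital planimetry and recorded as" cm². So every outcome above has a recorded starting value.
- **Statistical considerations** sets the general summary: "Continuous data will be presented as mean and standard deviations with confidence intervals of 95" per cent. It adds: "Where data is not normally distributed, non-parametric tests will be utilised as applicable".
- On adjustment, the same section says: "Further subgroup and regression analyses will be undertaken to adjust for confounding variables known to affect ulcer healing including age, duration, mobility and size". Ulcer size is on that list. Baseline VCSS and baseline EQ5D are not.
- The significance rule is a p "value of < 0.05 will be deemed significant".
- For numbers, "we aim to recruit 30 patients to each trial arm", with "participants allocated to one of two parallel groups in a 1:1 fashion" (Statement of design).

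**The concern.** Two features of the stated methods fit these outcomes poorly.

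**VCSS and EQ5D.** Subtracting the baseline is not the same as adjusting for it. With equal SDs at the two visits, a simple difference in mean change removes the full baseline difference between arms, whereas regression to the mean calls for removing only a fraction r of it. The comparison is then noisier than it need be, and a chance difference at the start pushes the estimate in the opposite direction. The collected baselines would prevent both, but the covariate list is tied to ulcer healing and names neither score.

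**Ulcer area.** A percentage reduction cannot exceed 100% and has no lower limit. An ulcer that grows from 1 to 4 cm² scores 100 × (1 − 4)/1 = −300%. Under a mean-and-SD summary, one such patient outweighs many good results.

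At stake are the interval widths for quality of life and clinical severity, and the value of the reported ulcer-area SD as planning information. The article says this phase should supply data for a refined sample size.

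**Working it through.** **The plan's own figure.** The only sample-size figure is for the later trial on time to healing. With a hazard ratio of 110/140 = 0.786 (exponential times), two-sided 5% and an assumed 80% power, the Schoenfeld formula gives 540 events, and 540 × 1.10 = 594. Both stated figures reproduce. They rest on time to healing, so nothing below affects them. The article gives no figure for VCSS, EQ5D or ulcer area.

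**Inputs.** From the article: 30 per arm, 1:1 allocation, significance level 0.05 (taken as two-sided). Assumed, because the article gives neither: the correlation r between baseline and follow-up, taken as 0.3 to 0.7, and equal SDs at both visits.

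**Precision, VCSS and EQ5D.** In units of the common variance:

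- change: 2(1 − r)
- follow-up or change with baseline as covariate (ANCOVA): 1 − r², ignoring the small cost of estimating one slope
- ratio: (1 − r²)/[2(1 − r)] = (1 + r)/2

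The detectable difference at 80% power is (1.96 + 0.84) × √(2 × variance/30).

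| r | Variance, change | Variance, ANCOVA | Ratio | Total N under ANCOVA matching 60 on change | Detectable difference, change | Detectable difference, ANCOVA |
|---|---|---|---|---|---|---|
| 0.3 | 1.40 | 0.91 | 0.65 | 39 | 0.86 SD | 0.69 SD |
| 0.5 | 1.00 | 0.75 | 0.75 | 45 | 0.72 SD | 0.63 SD |
| 0.7 | 0.60 | 0.51 | 0.85 | 51 | 0.56 SD | 0.52 SD |

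**Sensitivity to the equal-SD assumption.** Let k be the follow-up SD divided by the baseline SD. The ratio becomes k²(1 − r²)/(1 + k² − 2rk). At r = 0.5:

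- k = 1.5: 1.6875/1.75 = 0.96
- k = 1/1.5: 0.333/0.778 = 0.43

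The gain can therefore be negligible or large.

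**Chance imbalance.** The baseline difference between arms has standard error √(2/30) = 0.26 SD, so 95% of trials fall within ±1.96 × 0.258 = ±0.51 SD. A difference above 0.3 SD in either direction has probability about 0.25. With equal SDs, a baseline difference d shifts the unadjusted change contrast by −(1 − r)d. For d = 0.3 SD the shift is 0.21, 0.15 and 0.09 SD at r = 0.3, 0.5 and 0.7.

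**One enlarging ulcer.** Take an assumed arm of 30 with 18 ulcers healed (100%) and 12 reduced by 60%.

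- Mean (1800 + 720)/30 = 84%, SD 20, median 100%.
- Replace one of the 60% values by −300%: mean (2520 − 60 − 300)/30 = 72%, SD 73, median still 100%.

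One patient moves the mean by 12 points and multiplies the SD by more than three. The median does not move.

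**The case against.** The strongest objection is that a list of outcomes is not an analysis model. A reader might infer that VCSS and EQ5D will be compared as raw, unadjusted changes. The article does not say so: it names no between-arm model for them, and a change outcome is fully compatible with ANCOVA, because change adjusted for baseline gives the same treatment effect as follow-up adjusted for baseline. The covariate list is also open-ended, and an analysis plan that is not shown may name the baselines. This stands, and it makes the loss conditional. What remains is that the statistical section does set out a method for continuous data and a purpose for adjustment, and as written neither leads to the own-baseline covariate.

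A second objection is that rank tests are planned for non-normal data, and values of 100% beside one of −300% are plainly non-normal. This also stands for the p-value. It does not rescue a reported mean, SD and interval. The planned regression on ulcer size is directed at healing and does not change how percentage reduction is summarised.

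Third, (1 + r)/2 needs equal SDs, and so does the statement that change over-corrects. The general condition is a slope r × k below 1: at r = 0.7 and k = 1.5 the slope is 1.05, and change slightly under-corrects. This stands, so the figures are given only under that assumption.

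Two further steps are tempting and are not supported. One is to prescribe a log-area model. The Discussion cites 76.3% and 85.6% healed at 24 weeks in an earlier trial, so many areas may be zero and the added constant would dominate. The other is to claim a biased economic result. The article says EQ5D will feed the health economics but gives no method.

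**Conclusion.** The point holds in conditional form and is of low severity. The outcomes are defined as changes and as a percentage reduction, the baselines are collected, and the stated methods do not name baseline VCSS or EQ5D as covariates. If changes are compared unadjusted, then with equal SDs and an assumed r of 0.3 to 0.7, adjustment would cut the variance by 15% to 35%, and a chance baseline difference of 0.3 SD would shift the estimate by 0.09 to 0.21 SD. Neither r nor the SDs is in the article, and unequal SDs can make the gain much smaller or larger. For percentage reduction, the weakness lies in the mean-and-SD summary; the planned rank tests largely protect the significance test. All of this concerns secondary outcomes of a 60-patient feasibility trial. The primary feasibility outcome and the 540/594 calculation are unaffected.

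**What to change.** Make two additions to Statistical considerations:

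1. Between-arm comparisons of VCSS and EQ5D, whether of the follow-up score or the change, include the patient's own baseline value of that score as covariate.
2. Percentage reduction in ulcer area is reported as median and quartiles, with a rank-based comparison between arms, in place of mean and SD.

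The cost is a few lines of text. Both scores and the ulcer area are already recorded at baseline, so no new data, visits or patients are needed.

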## Trial population

### Inclusion criteria

Consenting patients, aged 18 and over, with ultrasound detected great or short saphenous venous incompetence with an associated primary or recurrent lower limb venous ulcer(s) will be eligible for inclusion. Saphenous reflux is defined as retrograde flow > 0.5 s in superficial vein [17].

### Exclusion criteria

Ankle-brachial pressure index < 0.8Previous inability to tolerate lower limb compression bandagingInability to provide informed consentPrevious lower limb arterial revascularisation procedureContrast allergyPrevious history of pelvic malignancy or pelvic radiotherapyCurrent pregnancyPrevious iliac vein interventionPrevious Saphenous vein interventionInfection in the previous 30 daysEstimated glomerular filtration rate (eGFR) < 60 ml/kg/minPerforator vein refluxLeg ulcer of non-venous aetiology (as assessed by clinician)Unfit for endovascular intervention based on history and examinationContraindications to anticoagulation

### Informed consent of the inpatient

The process of obtaining informed consent will be conducted in compliance with the principals of good clinical practice and requirements of the approving research ethics committee. Consent to enter the trial will be sought from each subject only after a full written and verbal explanation has been given and appropriate time allowed for consideration. The consent process will be conducted by the trial investigators in all cases. Signed subject consent will be obtained and stored in the medical notes. It is a right of the subject to refuse to participate or to withdraw at any time from the protocol without giving reasons and without prejudicing treatment.

#### Informed consent of the outpatient

Eligible patients will be given an information sheet at their outpatient visit and the trial will be explained to them by a team member. An anaesthetic pre-assessment visit will be conducted if applicable. Written informed consent will be obtained immediately before the procedure by an investigator.

### Randomisation

Following the consent process randomisation will be undertaken using sequentially numbered opaque sealed envelopes administered by an independent research assistant in the Lambe Institute, University Hospital Galway, allowing for allocation concealment. A unique trial number will be assigned to each individual at the time of randomisation. Patients will be randomised to one of two groups.

Group 1: Compression bandaging and endovascular treatment of saphenous truncal incompetence.

Group 2: Compression bandaging, endovascular treatment of saphenous incompetence with simultaneous iliac vein interrogation with IVUS and stenting if an occlusive lesion > 50% is identified.

A designated member of the research team who will not be involved with data collection will have access to the randomisation data and arrange intervention and investigation as required. There will be no sham intervention.

### Baseline patient data

Patients will all have a full medical history taken and clinical examination as part of their standard care. The following will be recorded:
WeightHeightBlood pressureHeart rateECGGenderEthnicityDate of birthDiabetes mellitusHypercholesterolaemiaHypertensionPrevious myocardial infarctionPrevious coronary revascularisationPrevious strokeAtrial fibrillationPeripheral arterial diseaseSmoking historyNYHA classBleeding historyHistory of deep venous thrombotic eventsObstetric historyMobility (scored 1–4; 1, full; 2, moderate—able to perform most everyday tasks with some impairment; 3, severe—can only mobilise very short distances such as bed to chair; 4, no mobility)Medication at time of consent (aspirin, clopidogrel, beta-blocker, calcium-channel antagonist, nitrates, cholesterol-lowering agent, ACE inhibitor/A2 receptor antagonist, insulin, metformin, sulphonylurea, warfarin)Duration of ulcer prior to enrolment in trialVenous Clinical Severity Score/EQ5D

#### Ulcer assessment

The ulcer will be evaluated by an assessor who has been blinded to the treatment allocation of the patient. Wound size will be calculated using digital planimetry and recorded as cm^2^. Wound assessment will be evaluated using the Bates-Jensen wound assessment tool which has been validated for use in venous leg ulcer assessment [18, 19]. Ulcers that heal prior to intervention will be analysed with intention to treat (Fig. 1).

**Fig. 1 Fig1:**
[figure not shown]
Schematic of study flow

#### Ankle-brachial pressure index

All patients in whom pedal pulses are impalpable will have an ankle-brachial pressure index calculated using a handheld Doppler and a manual sphygmomanometer.

#### Duplex ultrasonography

As part of routine clinical care, all patients with a venous leg ulcer undergo a lower limb venous duplex ultrasound. This will assess both the deep and superficial venous systems of the affected leg. The results from this scan will be used as the baseline pre-treatment lower limb duplex result.

#### Feasibility data

The number of eligible patientsThe number of consenting patientsThe number of patients declining participationAssessment of the number of patients who attend or miss scheduled follow-upReasons for missed follow-up appointmentsBarriers to timely scheduling of interventions and follow-up

## Interventions

### Endovenous ablation and IVUS procedure

All procedures will be carried out by either a vascular surgeon or interventional radiologist with significant experience in both endovenous ablation and IVUS (Visions 0.035, Philips, Amsterdam). The aim is for ablation within 4 weeks of randomisation. All patients will undergo endovenous ablation of refluxing axial superficial veins in the affected leg using thermal or non-thermal ablative techniques under local anaesthesia. Modality of intervention will be at the discretion of the operator. Control procedures will be undertaken in an ambulatory care setting while the interventional group will be managed in an operating theatre or interventional suite. All procedures will be completed under local anaesthesia.

The ablation procedure will be performed simultaneously with IVUS and stenting where applicable. A 9F access sheath will be placed under ultrasound guidance in the saphenous vein at the lowest point of reflux to allow introduction of firstly the IVUS catheter into the ipsilateral common iliac, external iliac and common femoral veins followed by the ablation probe. If the IVUS cannot be passed, the common femoral or jugular vein will be cannulated at the discretion of the operator. Iliac vein interrogation using the IVUS will be undertaken to determine the degree of area luminal area reduction (LAR) at each of the known arterial and ligamentous crossing points on the affected side which predispose to NIVL formation. These include the left and right proximal common iliac veins (where crossed by the right iliac artery), the right and left proximal external iliac vein (where crossed by the external iliac arteries and the retro-inguinal regions.

The LAR will be determined by comparison of the minimal luminal area at the NIVL site to the anatomical minimum for the respective vein, as recommended by experts in the field [22]. Area will be calculated using the standard mathematical formula Area = *A* = *πr*^2^. The reference area values for the iliac veins and the common femoral veins are detailed in Table 1. Lesions will be classified into the degree of stenosis by luminal area as detailed in Table 2.

**Table 1 Tab1:** Normal anatomical reference values for deep veins

Vein	Normal minimum diameter	Normal minimum area
**Common iliac vein**	16 mm	201 mm^2^
**External iliac vein**	14 mm	154 mm^2^
**Common femoral vein**	12 mm	113 cm^2^

**Table 2 Tab2:** Degree of stenosis based on luminal area

Vein	< 20% stenosis	20 to 49% stenosis	50 to 69% stenosis	> 70% stenosis
**Common iliac vein**	≥ 161mm^2^	160 to 103 mm^2^	102 to 62 mm^2^	≤ 61 mm^2^
**External iliac vein**	≥123mm^2^	122 to 79 mm^2^	78 to 48 mm^2^	≤ 47 mm^2^
**Common femoral vein**	≥ 90 mm^2^	89 to 58 mm^2^	57 to 35 mm^2^	≤ 34 mm^2^

Patients with a stenosis < 50% on the affected side will not have any further iliac or common femoral vein procedure performed. They will undergo endovenous ablation via the previously placed sheath in the great saphenous vein at the knee. Patients with a lesion > 50% will undergo iliac vein stenting with subsequent great saphenous ablation. The venous stent utilised will be at the discretion of the operator to broaden applicability. All residual varicosities shall be treated with foam sclerotherapy using 1% polidocanol. Foam will be standardised with 1:4 polidocanol to air ratio with 2 ml’s administered to each varicosity. Post-operatively those undergoing venous stenting will be placed on a three-month course of a novel oral anticoagulant.

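### The IVUS lumen area that decides stenting is fixed as πr² with no radius defined, and Table 2's 50 to 69% class starts slightly below a 50% reduction

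*Protocol article*

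**What the plan says.** All of this is in the protocol article, section Endovenous ablation and IVUS procedure, including Tables 1 and 2.

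- **Where the lumen is measured:** "at each of the known arterial and ligamentous crossing points on the affected side which predispose to NIVL formation". One site, for example, is the proximal common iliac vein "where crossed by the right iliac artery".
- **What is compared:** "The LAR will be determined by comparison of the minimal luminal area at the NIVL site to the anatomical minimum for the respective vein".
- **How area is obtained:** the next sentence reads "Area will be calculated using the standard mathematical formula" and gives A = πr². It does not say whether r comes from the smallest, largest or mean diameter, or from the area itself. The section gives no tracing or two-axis method for the vein. Digital planimetry is named only for the ulcer (first Ulcer assessment section).
- **Reference values:** Table 1 lists a normal minimum diameter and area for each of three veins. Table 2 turns the areas into four classes of stenosis.
- **Decision rules:** "Patients with a stenosis < 50% on the affected side will not have any further iliac or common femoral vein procedure performed", and "Patients with a lesion > 50% will undergo iliac vein stenting with subsequent great saphenous ablation". The abstract and the Randomisation section also use more than 50%.

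**The concern.** The formula πr² needs a single radius, and only a circular lumen has one. At a point where an artery or ligament crosses the vein, the plan gives no ground for assuming a circle. If the lumen is not circular, two operators who see the same frame can choose different diameters and report different LARs, possibly on opposite sides of 50%.

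LAR decides which Group 2 patients receive a stent, and those patients then also receive the post-stent anticoagulant course. It therefore drives the secondary objective and outcome on how many patients need stenting. It is presumably also the IVUS reference for the duplex comparison. The feasibility phase is meant to supply baseline data for a refined sample size, and the share of Group 2 actually stented is a natural input. With about 30 patients planned for that group, each patient moved across the limit shifts the share by 1/30 = 3.3 percentage points.

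Table 2 adds a second difficulty that does not depend on lumen shape: its class boundary does not sit at the 50% used in the text.

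**Working it through.** **1. Reproduce Table 1.** With A = π(d/2)² and the stated diameters of 16, 14 and 12 mm:

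- common iliac: π·8² = 201.06 mm² (stated 201)
- external iliac: π·7² = 153.94 mm² (stated 154)
- common femoral: π·6² = 113.10 mm² (stated 113; the unit is printed as cm², but the arithmetic and Table 2 show mm²)

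The reference areas are therefore areas of circles.

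**2. Error of πr² for a non-circular lesion.** *Assumption:* the lumen is an ellipse with long diameter a, short diameter b and axis ratio k = a/b. The documents give neither a shape nor a ratio, so a range is shown. The true area is πab/4. The ratio of πr² to the true area is:

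- r from the short diameter: 1/k
- r from the long diameter: k
- r from the mean diameter: π((a+b)/4)² ÷ (πab/4) = (1+k)²/(4k)

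The formula reads exactly 50% when the true area is 0.5 ÷ ratio of the reference. True stenoses between that point and 50% are misplaced.

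| k | Ratio: short / long / mean | Short: true stenosis reading above 50% | Long: true stenosis reading below 50% | Mean: true stenosis reading below 50% |
|---|---|---|---|---|
| 1.5 | 0.67 / 1.50 / 1.04 | 25-50% | 50-67% | 50-52% |
| 2 | 0.50 / 2.00 / 1.13 | 0-50% | 50-75% | 50-56% |
| 3 | 0.33 / 3.00 / 1.33 | 0-50% | 50-83% | 50-62.5% |

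For the mean radius: 0.5/1.0417 = 0.480, 0.5/1.125 = 0.444 and 0.5/1.333 = 0.375 of the reference area remain, so the limits are 52%, 56% and 62.5%. The error is nil if k = 1 or if r is derived from the measured area.

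Two illustrations for the common iliac vein (reference 201 mm²):

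- 18 x 5 mm (k = 3.6): true area π·18·5/4 = 70.7 mm², LAR 64.8%. The mean diameter gives π·11.5²/4 = 103.9 mm², LAR 48.3%. The short diameter gives 19.6 mm², LAR 90.2%. The long diameter gives 254.5 mm², more than the reference.
- 16 x 9 mm (k = 1.8): true area 113.1 mm², LAR 43.7%. The short diameter gives 63.6 mm², LAR 68.3%. The mean diameter gives 122.7 mm², LAR 38.9%.

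The first lumen is moved below 50% by the mean diameter, and the second is moved above 50% by the short diameter.

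**3. Table 2 against the 50% rules.** Reduction = 1 − area/Table 1 area, at the upper end of the 50 to 69% class:

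| Vein | Class starts at | Reduction | Area at 50% | Gap |
|---|---|---|---|---|
| Common iliac | 102 mm² | 1 − 102/201 = 49.3% | 100.5 mm² | 1.5 mm² |
| External iliac | 78 mm² | 1 − 78/154 = 49.4% | 77.0 mm² | 1.0 mm² |
| Common femoral | 57 mm² | 1 − 57/113 = 49.6% | 56.5 mm² | 0.5 mm² |

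The boundaries match a cut at 49% (0.51 x 201 = 102.5; 0.51 x 154 = 78.5; 0.51 x 113 = 57.6). A 102 mm² common iliac lumen is thus in the 50 to 69% class by the table and below 50% by calculation. The two text rules are strict on both sides, so a reduction of exactly 50% is under neither. The class labelled above 70% has the same slip (61, 47 and 34 mm² are 69.7%, 69.5% and 69.9%), but no stenting decision hangs on it.

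**The case against.** The strongest reply is that the πr² sentence only explains Table 1. It stands immediately before the sentence that introduces that table and reproduces its three areas exactly, while the lesion quantity is already called an area obtained by IVUS. On that reading the lesion method is merely unstated, as a condensed article may leave it. This reading is possible. But the text does not limit the formula to Table 1: the sentence is prospective and follows directly on the definition of the lesion comparison. A specific formula that can be applied wrongly is more than an omission.

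A reader might infer that the veins are flattened at these sites, so that lesions will be misclassified. The documents do not support that. They name crossing points but no lumen shape, and the Trial rationale describes the lesions as adhesions, membranes or webs inside the vessel. The direction of error is also open because r is undefined. At modest axis ratios the mean radius misplaces only a narrow band, and the 18 x 5 mm example is a strongly elongated one. The long-diameter result, a lesion larger than the normal vein, would probably be noticed.

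A reader might also infer that the number stented becomes uninterpretable, or that the trial's main results are compromised. Neither follows. The number stented remains a direct count of what operators did under the protocol. The primary feasibility outcome is agreement to randomisation, and healing is compared between randomised groups by intention to treat; neither is calculated from LAR.

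On Table 2, the gaps are under one percentage point, and one can argue that the table governs because the text refers to it for classification. The text nevertheless states its rules in percentages, so the conflict stands, though it is small.

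**Conclusion.** Wrong as written, of moderate to minor weight.

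- **Formula.** The protocol fixes luminal area as πr² with r undefined, on a plain reading also for the lesion. *If* the lumen is not circular, a single minimum, maximum or mean radius can misstate LAR and move lesions across 50% in either direction. With the mean radius and an assumed ellipse, the area is overstated by 4%, 13% and 33% at axis ratios of 1.5, 2 and 3. How many patients this would affect cannot be computed from the documents.
- **Table 2.** Its 50 to 69% class starts at reductions of 49.3%, 49.4% and 49.6%, and exactly 50% is covered by neither text rule. This holds under either reading of the formula and needs no shape assumption.

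The effect is confined to who in Group 2 is stented and to the secondary results that rest on it, chiefly the number stented. The primary feasibility outcome is untouched.

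**What to change.** 1. Limit the πr² sentence to the origin of the Table 1 reference areas. State that the lesion's smallest lumen area is measured directly on the acquired IVUS frame, for example by tracing the border, and that the longest and shortest diameters are recorded as well. Calculate LAR from the measured area. If another method is already in use, name it and define r.
2. Recompute the Table 2 boundaries from Table 1, correct the common femoral unit, and reconcile the table with the percentage rules in the text so that every value, including exactly 50%, falls in one class. Which limit applies is for the investigators to decide.

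The cost is protocol wording, one more CRF field and a little extra measurement time per site; the documents give no figure for that time.
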